#### Quality control

To minimize interrater variability, we will regularly conduct co-evaluation of patients with main focus on rating scales. Two research assistants will participate in a full participant inclusion and will individually be diagnosing and rating the participant. Any discrepancies will be noted and discussed with a specialist in psychiatry.

#### Validation of diagnosis – case definition

In accordance with the NOS, the gold standard for an adequate case definition is independent validation. All patients will be evaluated by SCAN interview. Additionally, patients who require hospital-based treatment (in- or outpatients) are evaluated by the treating psychiatrist in the clinic before referral to the study. Patients who are not treated at in- or outpatient facilities of the psychiatric hospitals (e.g. followed by a private psychiatrist) will be either independently evaluated by an experienced psychiatrist who will watch the video recording of the SCAN interview or by consensus diagnosis with an experienced specialist in psychiatry. The SCAN interviewer will not be blinded to patient status or diagnosis.

#### Follow-up

The patients will be invited to a follow-up visit after one to two years after enrolment. This follow-up visit is planned to include all the same measurements (including blood and CSF measurements) as for the primary visit and a Questionnaire about the Process of Recovery (QPR) will be added [60]. By the follow-up assessment we expect to collect data that can enhance the understanding of the association between neuroinflammation and depression/depressive symptoms. Furthermore, trajectories of neuroinflammatory markers will be addressed by follow-up of later psychiatric diagnoses in the well validated Danish registers, also for participants who do not attend follow-up visit, in order to search for predictors of disorder progression. We will in detail conduct an analysis plan for the analyses of the follow-up assessments before the end of follow-up inclusion and prior to data analyses.

#### Biological samples and measures

To minimize the impact of diurnal variation all samples are to be collected between 8.30 a.m. and 01.00 p.m.

#### Blood samples

Venous blood samples will be collected prior to lumbar puncture and we aim to have ≥90% of blood samples collected between 9.30 and 11.30 a.m. Prior to the blood sample, a skin swab is performed and stored at −80°C for quality control analyses. A maximum of 44 mL of blood will be sampled; 8 mL used for initial analyses and 36 mL stored for later use. For a detailed description of blood sample drawing and equipment, see eSupplementary Paragraph 4.1.

#### Cerebrospinal fluid samples

The lumbar puncture will be carried out according to current consensus [61], and we aim to have ≥90% of CSF samples collected between 10.00 a.m. and 12.00 p.m. We furthermore aim for the time from collection of blood samples to collection of CSF samples to not exceed 35 min for ≥90% of participants. In brief, the participant will preferably be placed in a lateral decubitus position. The L3/L4 or L4/5 space will be identified, and local anesthesia will be given in the form of a sufficient amount of lidocaine (depending on the size of the participant). Prior to the lumbar puncture, a skin swab will be performed and stored at −80°C for quality control analyses. The lumbar puncture will be carried out preferably using an atraumatic 22G needle. Two mL will be taken for routine examination and 14 mL will be stored in the biobank for later analysis. The samples are to be analyzed as fast as possible and within 1 h from the first droplet of CSF. For details regarding the lumbar puncture, procedure and equipment see eSupplementary Paragraph 4.2.

#### Procedures for biobank storage

Thirty-six mL of blood and 14 mL of CSF will be used for biobank storage and will be stored both on filter papers and portioned in 0.5 ul aliquots after centrifuging at 1145 G for 10 min. For further details of blood and CSF storage procedures, see eSupplementary Paragraph 4.3.

#### Measures of safety regarding lumbar puncture

In order to assess the risk of adverse events associated with lumbar puncture, participants are contacted on the day after the intervention. All symptoms that could be due to the procedure are noted with specific focus on possible post lumbar headache and infections.

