**Fig. 1 Fig1:**
[figure not shown]
Recruitment, inclusion and follow-up. Patients will mainly be recruited from the Referral and Diagnostic Department and healthy volunteers from internet advertisement. Before any examination, the participant will sign the informed consent formula. A variety of potential confounders will be registered by questioning or questionnaires (including body-mass index (BMI), smoking status, current psychotropic and other medication, non-steroid anti-inflammatory drugs (NSAID), alcohol, eating and exercise habits and more). Contraindications to lumbar puncture will be evaluated. Prior to lumbar puncture a neurological examination including neurological evaluation scale to assess neurological soft signs will be performed and blood samples drawn. After the lumbar puncture the WHO Schedules for Clinical Assessment in Neuropsychiatry (SCAN) interview will be conducted (SCAN interview will be conducted prior to lumbar puncture for healthy participants to rule out prior and current psychiatric symptoms). Cognitive testing includes Brief Assessment of Cognition in Schizophrenia (BACS), Montreal Cognitive Assessment (MoCA), Mini-Mental State Examination (MMSE) and Trail Making Test (TMT) A and B. Questionnaires with self-rating of depressive symptoms (Major Depression Inventory (MDI)), quality of life (EQ-5D-5L), diet and exercise will be filled in by the participant. After the visit the following rating scales will be evaluated by the research assistant: Symptom rating (depressive symptoms: Hamilton depression rating scale – 17 items (HAMD-17)/−6 items (HAMD-6) and Montgomery-Asberg Depression Rating Scale - 10 items (MADRS-10)/− 6 items (MADRS-6), manic symptoms: Young Mania Rating Scale (YMRS), anxiety symptoms: Hamilton Anxiety Rating Scale (HAM-A) and psychotic symptoms: Positive and Negative Symptom Scale (PANSS) and Scale for Assessment of Positive/Negative Symptoms (SAPS/SANS)) and functioning by Personal and Social Performance Scale (PSP) and Global Assessment of Functioning. Fecal samples will be collected at home. The participant will be followed up the day after the intervention for the registration of possible side effects. All biological samples will be stored in a biobank for later laboratory analyses. The participant will be followed up after one-two years with repetition of all measurements

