### Risks and side effects

Lumbar puncture is a commonly used procedure for diagnostics of CNS disorders and serious complications are very rare with the most common side effects being backache, nerve root irritation and headache, while infections are described only in case reports [32]. By using the atraumatic needle, the risk of inducing post lumbar puncture headache is reduced to approximately 4% [71]. We consider the procedure to be safe when carried out by a trained physician after a comprehensive neurological evaluation and screening for contra-indications. The day after the lumbar puncture, the participant will receive a phone call and any side effects will be registered. If the participant experiences severe post lumbar puncture headache, the participant will be admitted to the nearest neurological department in accordance with current practice in the Capital Region of Denmark.

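### Lumbar-puncture risk is to be assessed from a single next-day contact, so events that begin later have no described route into the count and the observed rate can only err downward on this account

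*Protocol article*

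**What the plan says.** Under Measures of safety regarding lumbar puncture, the article gives the purpose of the safety contact: "In order to assess the risk of adverse events associated with lumbar puncture". The method follows in the same sentence: "participants are contacted on the day after the intervention". All symptoms that might be due to the procedure are to be noted, "with specific focus on possible post lumbar headache and infections".

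Two other places describe the same contact. The Fig. 1 legend says: "The participant will be followed up the day after the intervention for the registration of possible side effects". Risks and side effects says: "The day after the lumbar puncture, the participant will receive a phone call and any side effects will be registered". That section also gives the expected frequencies. With an atraumatic needle the headache risk is put at about 4%, "while infections are described only in case reports".

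The next study contact described is under Follow-up: "The patients will be invited to a follow-up visit after one to two years after enrolment". That visit is to repeat the baseline measurements and add a recovery questionnaire. It is not said to ask about adverse events of the first puncture.

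**The concern.** The stated aim is a risk, that is, the proportion of participants who have an adverse event because of the puncture. The method observes only what has begun by one contact the next day. Under Cerebrospinal fluid samples, at least 90% of CSF samples are planned for late morning (10.00 to 12.00), so the window is roughly one day. An event with onset after the call is not described as being recorded anywhere.

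What is at stake is the meaning of any safety figure the study produces. A rate observed up to the next-day contact is a different quantity from the risk of the procedure. Set beside the cited 4%, it could look favourable partly because of its shorter window. The study punctures at least 100 patients and at least 100 healthy volunteers, and plans to repeat the procedure, so its own safety count should be labelled for what it is. The efficacy-type inference on CSF markers, cytokines and autoantibodies is not touched.

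**Working it through.** The article states no precision target or sample size for puncture safety, so there is no figure of its own to reproduce. The check has two parts.

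**1. Is there any other described route for late events?**

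- Measures of safety, the Fig. 1 legend, and Risks and side effects all give one contact on the day after the puncture. They agree, so this is not a slip in one place.
- Follow-up (one to two years): no collection of adverse events from the first puncture is stated.
- Risks and side effects: severe headache leads to admission, with no time limit, but no step is stated that registers such an admission in the study's safety data.
- Registry data: future medical history is to be obtained from the Danish registers. The listed uses are socioeconomic factors, infections, comorbidity, treatment outcome and later psychiatric diagnoses. Puncture safety is not among them.

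A severe late event might surface through the last two routes, but neither is said to feed the count. For milder late events no route is described.

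**2. How large could the effect be for headache?**

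Inputs:
- N = 200, the minimum enrolment of 100 + 100 (Study design), counting the baseline puncture only.
- p = 0.04 (Risks and side effects).
- f = share of headaches that begin after the call. The article gives no onset times, so f is purely an assumption.

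Formulas:
- Expected headaches = N × p = 200 × 0.04 = 8.
- Expected missed = N × p × f.
- Observed rate = p × (1 − f).
- Probability of missing at least one = 1 − (1 − p × f)^N.

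| Assumed f | Expected missed | Observed rate | P(at least one missed) |
|---|---|---|---|
| 0% | 0 | 4.0% | 0% |
| 10% | 0.8 | 3.6% | 55% |
| 20% | 1.6 | 3.2% | 80% |
| 30% | 2.4 | 2.8% | 91% |
| 50% | 4.0 | 2.0% | 98% |

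For example, at f = 10%: 200 × 0.04 × 0.10 = 0.8 missed; 0.04 × 0.90 = 3.6%; 1 − 0.996^200 = 55%.

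For scale, the exact 95% confidence interval for 8 of 200 is 1.7% to 7.7%.

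**Direction.** Since f cannot be negative, onset timing can lower the observed rate or leave it unchanged. It cannot raise it.

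**Infection.** The article gives no rate and says infections are known only from case reports. The expected number in 200 participants is then close to zero under any observation window, and no numerical under-count can be shown.

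**The case against.** The strongest reply is that the article nowhere says that headache or infection begins after the next day, so the size of any loss rests on an assumption. This stands. It rules out saying that the study will under-count; the text supports only that it can, by an unknown amount. It does not remove the structural gap, because a risk is to be assessed and onset after the call has no described route into the data.

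The second reply is that the effect is small and concerns no outcome. Every illustrated rate (2.0% to 4.0%) lies inside the 1.7% to 7.7% interval, and Table 1 and the secondary outcomes contain no safety endpoint or safety paper. This also stands and sets the severity. It does not make the window harmless, because a one-sided bias is not part of sampling error and would not shrink with more participants.

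The third reply is that this is a condensed article. The lumbar-puncture procedure, the time schedule and the participant information are referred to supplementary paragraphs that are not shown, and one of these may describe a later contact or an instruction to report late symptoms. If so, a reference to it in the safety paragraph would settle the point. As printed, however, three places give the next-day contact as the means of registration and none points to anything later.

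Three stronger readings are tempting, and the article does not support them:

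- A reader might infer that understated study rates would inform consent for the second puncture. Ethical considerations ties participant information to the risks listed under Risks and side effects, where the headache figure comes from the literature and not from this study.
- A reader might infer that the call is the only trigger for the severe-headache pathway. That sentence is not conditional on the call and has no time limit.
- A reader might infer that next-day rates will be published as the risk of the procedure. The article does not say how, or whether, safety rates will be reported.

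**Conclusion.** The point holds in a limited form. The article says it will assess the risk of lumbar-puncture adverse events, but the only ascertainment it describes ends with one contact the next day. Events that begin later have no described route into the count, so with respect to onset timing the observed rate can only be biased downward.

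The amount is unknown. At 4% and 200 participants, assumed late-onset shares of 10%, 30% and 50% would turn a true 4.0% into an observed 3.6%, 2.8% and 2.0%, with 0.8, 2.4 and 4.0 of 8 expected cases missed. These figures rest on the cited 4%, minimum enrolment, and late-onset shares that have no source in the article. For infection, a named focus of the contact, only the absence of described observation after the next day can be noted.

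Severity is low. No primary or secondary outcome depends on this count, and the unseen supplement may already close the gap.

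**What to change.** Keep the next-day call. Add one brief automated query some days later, as a text message or a form in the REDCap database already in use, that asks about symptoms that began after the call and records their onset date. The article offers no basis for a particular interval, so the investigators should choose it and state it. With onset dates recorded, the rate up to the next-day contact and the rate over the longer window can both be reported. If the supplement already describes such a step, cite it in the safety paragraph.

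If no query is added, describe any reported figures as events up to the next-day contact and do not present them as the risk of the procedure.

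The cost is one extra message per participant, a line in the protocol, some additional reports to handle and possibly a higher stated rate. No extra procedure is needed, and clinical management, outcomes and sample size do not change.

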#### Fecal samples

Each participant is asked to provide a fecal sample, either during the inclusion, or afterwards from home. Fecal samples are collected in two ways, both in a Sarstedt tube (Sarstedt, Bording, Denmark) and by using the OMNIgene•GUT OMR-200 Sample Collection Kit (DNAgenotek™, Ottawa, Ontario, Canada). If collected at home, the fecal samples will be sent by mail, and then stored in the freezer at − 80 degrees Celsius. Samples done during the visit will be frozen immediately. A score on the Bristol Stool Scale [62], time and date of sampling, as well as time and date of freezing is to be noted. Freeze/thaw cycles are avoided. Since gut microbiota research is fast developing, a detailed analysis plan for the gut microbiota samples is planned to be conducted later on before finishing the longitudinal collection of samples prior to analyses.

#### Other biological measures

Blood pressure and pulse will be measured prior to the neurological examination.

#### Registry data

We will use the Danish registers to obtain information on socioeconomic factors and prior, current and future medical history, such as prior infections treated in the primary care sector, comorbidities, treatment outcome (e.g., psychiatric readmissions and change in medication) and later psychiatric diagnoses.

#### Data storage

All data will be kept in secured folders and in the database RedCap [63, 64] in accordance with approval from The Danish Data Protection Agency. Written consent formulas will be kept in a locked locker in a locked office, and additionally stored electronically in secured folders. For more detailed information on data storage and pseudonymization see eSupplementary Paragraph 4.4.

#### Biological sample storage

All cryo vials will be placed at − 80 degrees Celsius as soon as possible, and time for freezing will be noted. The filter papers will be left to dry overnight at room temperature and placed at − 80 degrees Celsius on the next day. For details see eSupplementary Paragraph 4.3. Fecal samples will be stored at − 80 degrees.

#### Laboratory analyses

All analyses will be run blinded by pseudonymization. Laboratory analyses will be performed according to a statistically designed experimental schedule based on a randomized block design or similar, to minimize the risk of confounding by time of analysis, batch and other factors.

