#### Immediate analyses

Eight mL of blood and two mL of CSF will be analyzed immediately at Rigshospitalet. Initial blood analyses include; white blood cell (WBC) count, erythrocytes, hemoglobin, platelets (Sysmex XN9000, Sysmex), high sensitivity CRP, IgG (cobas® 8000 modul c502, Roche), albumin, glucose (cobas® 8000 modul c702, Roche) and HbA1c (Tosoh G8, Sysmex). Initial CSF analyses include; WCC (Sysmex XN9000, Sysmex), differential count (DM96, CellaVision), albumin, IgG, total protein (cobas® 8000 modul c502, Roche), erythrocytes (Sysmex XN9000, Sysmex), glucose and lactate (ABL800 FLEX, Radiometer).

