#### Primary outcome analyses

CSF total WCC, CSF/serum albumin ratio, CSF total protein and IgG index will be analyzed immediately as described above. IgG index is calculated by the following formula:$$\frac{CSF_{IgG}/{Blood}_{IgG}}{CSF_{Albumin}/{Blood}_{Albumin}}$$

CSF Cytokines are planned to be analyzed using the V-plex Neuroinflammation Panel 1 Human Kit from Meso Scale Diagnostics. CSF and blood CNS-reactive autoantibodies are planned to be analyzed by Autoimmune Encephalitis Mosaic 1 and GAD65 panels from Euroimmun.

Primary and secondary outcomes for gut microbiota analysis are yet to be defined due to the fast development of gut microbiota research. However, a detailed analysis plan including well defined primary and secondary outcomes for gut microbiota samples will be conducted prior to finishing the longitudinal collection of samples.

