### Statistical analysis plan

Power and sample size calculations are based on two-sample *t*-tests using standardized mean differences (SMDs) and based on not yet published results from a meta-analysis from our group comparing patients with unipolar depression to healthy controls. If all values are observed above the lower limit of quantification (LLOQ), we expect the power for CSF/serum albumin ratio and CSF total protein to be high (95% or higher), whereas the power for IgG index and CSF total WCC are expected to be low (< 50%) though effect sizes in previous studies are heterogenic. For IL-6 we expect good power (> 80%), but low power for IL-8 (< 50%).

Based on previous studies we expect a proportion of biomarker measurements to be lower than LLOQ, most pronounced in the control group. By simulation, we found that given an effect size leading to a power of 80% without censoring, 33% censoring will only reduce power with a maximum of 5%, while 50% censoring will only reduce power with a maximum of 10%, when using the censored Gaussian model (see eSupplementary for further details).

Regarding CNS-reactive autoantibodies the current evidence of expected findings in CSF from healthy controls is very limited. We expect no positive CNS-reactive autoantibodies in the CSF among control subjects [24] and a previous study found no CNS-reactive autoantibodies in CSF from patients either [65]. However, 0.23% of healthy controls [24] and 0.4% of patients with affective syndromes [65] had measurable CNS-reactive autoantibodies in blood.

Linear models will be applied for comparison of all continuous primary outcomes adjusting for sex and age. All continuous outcomes being measured as concentrations or ratios will be log-transformed before analysis (if zeroes are present, a small value, estimated by profile maximum likelihood, will be added to all observations prior to analysis [66]). If values of an outcome are observed below LLOQ, we will use the censored Gaussian model instead of the linear model.

Pearson chi-square test without adjustment for continuity will be applied for analyses of CNS-reactive antibodies. All results of primary and secondary analyses will be reported with the effect size, 95% confidence intervals and *p*-values. Two-sided tests with *p* < 0.05 will be considered significant. All analyses will be done in the program R version 4.0.5 [67] or later using the package “survival” [68] to fit the censored Gaussian model.

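### The block-randomised assay schedule is missing from the IL-6 and IL-8 models, and it cannot set the assay order of the four co-primaries that are measured immediately

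*Protocol article*

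**What the plan says.** Under Laboratory analyses, the protocol article states: "Laboratory analyses will be performed according to a statistically designed experimental schedule based on a randomized block design or similar". The stated purpose is "to minimize the risk of confounding by time of analysis, batch and other factors". No assay is exempted.

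Under Statistical analysis plan: "Linear models will be applied for comparison of all continuous primary outcomes adjusting for sex and age". If values fall below the lower limit of quantification, "we will use the censored Gaussian model instead of the linear model". No block, plate, batch or calendar term is named for either model.

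Under Primary outcome analyses: "CSF total WCC, CSF/serum albumin ratio, CSF total protein and IgG index will be analyzed immediately as described above". The section on immediate analyses adds: "Eight mL of blood and two mL of CSF will be analyzed immediately at Rigshospitalet". The section on cerebrospinal fluid samples sets the time limit: "The samples are to be analyzed as fast as possible and within 1 h from the first droplet of CSF". The cytokines are not on the immediate list. They are to be run with a commercial multiplex kit, and most of the CSF is stored in the biobank for later work, so their run order can be scheduled.

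**The concern.** There are two separate mismatches between the stated laboratory design and the stated analysis.

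1. **IL-6 and IL-8.** If samples are allocated to plates or batches by blocked randomisation, the block is a design factor. A model with sex and age only leaves the plate-to-plate variance in the residual. The group difference is already free of that variance when blocks are balanced, but the reported standard error still includes it. Precision that the design has secured is then not used in the confidence intervals and p-values.

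2. **White cell count, albumin ratio, total protein and IgG index.** These are four of the six continuous co-primaries and make up the whole primary set of the neuroinflammation paper. They are run on fresh samples, so the date of assay is the date of the visit. A laboratory schedule cannot randomise that order, and the sex-and-age model does not replace the missing protection against time and batch. Controls on the hour of sampling deal with diurnal variation, not with calendar drift in instrument, calibration or reagent lot.

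**Working it through.** The article gives no plate variance, number of plates or drift, and it does not print the standardised mean differences (SMDs) behind its power statements. There is therefore no figure of its own to reproduce, and everything below shows size under stated assumptions.

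**Inputs from the article:** 100 per group (minimum); two-sided 5% test; sex and age the only covariates.

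**Anchor (assumption):** an effect with 80% power at 100 per group and no plate effect. By the exact t-test this is an SMD of 0.398 (normal formula 0.396).

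**Part 1: block omitted for IL-6 and IL-8**

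Assume 10 balanced blocks of 10 patients and 10 controls, with plates explaining a share r of the total variance (set to 1).

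- True variance of the group difference: (2/100)(1 − r), because plate effects cancel within balanced blocks.
- Variance that the model without blocks estimates: (2/100)[(1 − r) + r × 90/99]. This is nearly the full variance.
- The effective critical value without blocks is therefore 1.972 × √{[(1 − r) + 0.909r]/(1 − r)}. With blocks it is 1.973 (189 degrees of freedom).
- Signal in true standard errors: λ = 0.398/√[0.02(1 − r)].

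| r | Critical value, no block | Type I error, no block | λ | Power, no block | Power, with block |
|---|---|---|---|---|---|
| 0.10 | 1.972 × 1.049 = 2.069 | 3.9% | 2.967 | Φ(0.898) = 81.5% | Φ(0.994) = 84.0% |
| 0.20 | 1.972 × 1.108 = 2.185 | 2.9% | 3.146 | Φ(0.962) = 83.2% | Φ(1.174) = 88.0% |

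A simulation of the same layout (20,000 runs, SMD 0.396) agrees. At r = 0.10, type I error is 4.0% without blocks and 5.0% with them, and power is 81.0% vs 83.5%. At r = 0.20, type I error is 3.2% vs 5.1%, and power is 82.7% vs 87.7%. At r = 0 the two models perform the same. The loss is thus about 2 points at a 10% share and about 5 points at 20%, and the test without blocks is conservative.

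**Part 2: the four immediate outcomes**

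The immediate-analysis statement and the one-hour limit for CSF together fix the assay date at the visit date. If an assay shifts once during recruitment by s standard deviations, and the shares of patients and controls measured after the shift differ by g, the bias is s × g. The standard error is √(2/100) = 0.1414. With x = s × g/0.1414, the false-positive rate is Φ(−1.96 − x) + Φ(−1.96 + x).

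| Shift s (assumed) | Gap g = 20% | g = 50% | g = 100% |
|---|---|---|---|
| 0.1 SD | 5.2% | 6.4% | 10.9% |
| 0.2 SD | 5.9% | 10.9% | 29.3% |
| 0.3 SD | 7.1% | 18.6% | 56.4% |

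Example: s = 0.2 and g = 20% give a bias of 0.04 and x = 0.283, so the rate is Φ(−2.243) + Φ(−1.677) = 0.0125 + 0.0468 = 5.9%.

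**The case against.** **The plate term is a detail for the full analysis plan.** An article may leave technical covariates to a fuller document, and the supplement is not shown. That would carry the point if the article were silent on the model. It is not: it names the covariates for all continuous primary outcomes and, separately, commits to a blocked design. Followed as written, the two do not match. What stands is that the consequence is limited. With balanced blocks there is no bias, and if plates do not differ there is no cost.

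**A reader might put the power gain at 4 or 8 points**, by comparing 80% with the 84% or 88% that follows from shrinking the standard deviation alone. That overstates it. Balanced blocking already reduces the true sampling variance of the unadjusted difference, so its power is about 82% or 83%, not 80%.

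**The block-design sentence was probably meant for stored samples.** The immediate analyses have their own subsection directly after it, and a designed schedule suits only assays whose order can be chosen. This is a fair reading, and the wording *or similar* is loose. The sentence nevertheless carries no such limit, and restricting it leaves the four immediate outcomes without a stated safeguard against calendar drift.

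**A reader might infer that drift does confound those four outcomes.** The article does not support this. It nowhere says that patients and controls are enrolled at different times, and silence on recruitment pacing is not evidence of separated calendars. A 29% false-positive rate from a 0.2 SD shift needs complete separation. Nor would drift act equally on all four outcomes: CSF and blood IgG are run on the same analyser module, so a shared proportional IgG shift would cancel in the IgG index. Blood and CSF albumin are on different modules, so the same cannot be assumed for albumin. The one-hour limit is also stated only for CSF; for blood the article says no more than that it is analysed immediately.

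**Conclusion.** The point holds in two limited parts.

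For IL-6 and IL-8, the stated model leaves out a factor that the stated design uses. If plates differ and blocks are balanced by group, the estimates stay unbiased, the standard errors are too large, and the test is conservative. The size rests on assumed plate shares of 10% or 20% and an effect with 80% power in the absence of plate effects. It would be wrong to read the omission as a source of false positive cytokine findings; only blocks unbalanced by group could produce bias, and nothing in the article suggests them.

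For the four immediate outcomes, protection against time and batch effects cannot come from a laboratory schedule, and the model does not supply it. Whether this matters in practice is open. The false-positive rate stays close to 5% under modest drift and small calendar gaps, and becomes serious only when the groups' calendars are far apart. The text supports a correction of scope and an adjusted analysis. It does not support a claim that these results are confounded.

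**What to change.** 1. Add plate or batch (the randomisation block) as a fixed or random effect in the IL-6 and IL-8 models, in both the linear and the censored Gaussian form.
2. Restrict the block-design sentence to the batched biobank assays.
3. For white cell count, albumin ratio, total protein and IgG index, adjust for calendar period or reagent-lot period, at least as a sensitivity analysis. This works where patients and controls overlap in time.

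The cost is a change of wording, the use of assay dates or lot records, and a few degrees of freedom: with 10 blocks the residual degrees of freedom in the layout above fall from 198 to 189. No change to the sample size or the assays is needed.
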